## Abstract

**Background:**

HIV-associated neurocognitive disorders occur in nearly 50% of adults with HIV. Such disorders can interfere with everyday functioning such as driving and medication adherence. Therefore, cognitive interventions are needed to address such neurocognitive disorders as well as improve everyday functioning, especially as people age with HIV.

**Objective:**

This article reports and discusses the overall rationale and development of speed of processing training, a computerized Internet cognitive training program, to improve this specific neurocognitive ability as well as everyday functioning and quality of life in adults aging with HIV. Although this protocol has been shown to improve speed of processing, everyday functioning, and quality of life in healthy, community-dwelling older adults in the advanced cognitive training in vital elderly (ACTIVE) study, its efficacy in adults aging with HIV has not been established. Nevertheless, such a cognitive intervention is particularly germane as 52%-59% of adults with HIV experience HIV-associated neurocognitive disorders (HAND), and both the frequency and severity of such disorders may increase with advancing age.

**Methods:**

The description of this longitudinal randomized controlled trial covers the following: (1) rationale for speed of processing training in this clinical population, (2) overview of overall study design, (3) eligibility criteria and HAND, (4) intervention dosage, (5) assessment battery, and (6) examination of biomarkers.

**Results:**

The project was funded in April 2016 and enrolment is on-going. The first results are expected to be submitted for publication in 2020.

**Conclusions:**

Similar novel cognitive intervention approaches are suggested as they may be of value to those with HAND and may utilize similar features of this current randomized controlled trial (RCT) protocol to examine their therapeutic efficacy.

**Trial Registration:**

ClinicalTrials.gov NCT02758093; https://clinicaltrials.gov/ct2/show/NCT02758093 (Archived by Webcite at http://www.webcitation.org/6p8C5fBCX)

## Introduction

Combination antiretroviral therapy (cART) has resulted in improved health-related outcomes and longer life in adults with human immunodeficiency virus (HIV), with some studies estimating length of life being tantamount to those without HIV [1]. Despite such optimism, neuroinflammation, substance abuse, stress, stigma, depression and anxiety, and poorer educational quality often associated with HIV may contribute to other poorer health-related outcomes such as neurocognitive impairment, often referred to as HIV-associated neurocogntiive disorders (HAND) [2]. HAND is an objective diagnosis determined by administration of a neurocognitive assessment measuring at least seven neurocognitive domains (eg, speed of processing, verbal memory). With such an assessment, when patients score greater than 1 standard deviation below their age and education norm on 2 or more neurocognitive domains, they are considered to have HAND; this classification rubric is referred to as the Frascati criteria [3]. Using the Frascati criteria, 52% to 59% of adults with HIV experience HAND [4]. Furthermore, there are gradations of HAND of increasing severity in terms of the neurocognitive and everyday functioning impairments, with ~33% experiencing asymptomatic neurocognitive impairment, ~12% experiencing mild neurocognitive disorder, ~5% experiencing mixed neurocognitive disorder, and ~2% experiencing HIV-associated dementia [5].

With such well documented neurocognitive impairments, neurocognitive aging in this group represents a major concern since by 2020, 70% of adults with HIV in the United States will be 50 years and older [6,7]. Thus, there is a growing population that is particularly vulnerable to HAND due to the cooccurrence with aging-related neurocognitive impairments as well as age-related comorbidities that likewise compromise brain health. For example, in a study of 162 older (50+ years) and younger (<50 years) adults with and without HIV, Vance and colleagues [8] found as a group, older adults experienced more neurocognitive impairments. Such neurocognitive impairments affect driving safety, medication adherence, instrumental activities of daily living, and quality of life [9-13]. Furthermore, in the cART era, these neurocognitive impairments continue to be observed in several domains including memory, executive functioning, and 1 area of particular importance—speed of processing [14-29].

Speed of processing is the rate at which neurocognitive functions are performed [30-32]. People with HIV are vulnerable to speed of processing declines [33,34], especially as they age [30-32]. In a meta-analysis of 41 HIV neurocognitive studies from both the pre- and post-cART era [33], speed of processing was among the neurocognitive domains demonstrating the greatest decline from early to late stages of HIV for all ages. More recent studies also show that speed of processing deficits are common and persist in the post-cART era [14-29]. In fact, a 2014 study of 186 adults with HIV found that speed of processing “fully mediated the effects of age on learning, memory, and executive functioning and partially mediated the effect of major depressive disorder on learning and memory” (p. 806) [35] while other HIV studies show speed of processing deficits impair real-world functioning [13,36]. Such speed of processing declines are associated with poorer driving performance and more at-fault crashes in healthy older adults [30,37,38] as well as middle-aged (40+ years) and older adults with HIV [10,13,39,40], which is a growing public health concern [10,13,39]. In the Southern United States, specifically in the Deep South, these points are highly relevant because (1) even with speed of processing declines, adults with HIV must rely on their own driving, especially in rural areas with limited public transportation; and (2) the epicenter of HIV has emerged here in the last decade [41,42], which means many adults with lower socioeconomic status backgrounds and African Americans with HIV will also have HAND [43,44]. Few behavioral interventions have aimed to improve neurocognition in this vulnerable population [45], and pharmacological cognitive interventions produce adverse side effects in a population already experiencing multiple comorbidities [45-50].

Fortunately, some types of computerized cognitive interventions have been shown to improve neurocognition without adverse side-effects [51-53]. Despite the known efficacy of computerized cognitive training programs, only 2 such studies have examined this in adults with HIV. One study attempted to improve global neurocognition in a mixed sample of 30 adults with and 30 adults without HIV; unfortunately, only 54% (25/46) of those assigned to the active condition were able to use the system successfully and probably as a result, no therapeutic neurocognitive benefit was derived [54]. Yet, in 1 study involving adults aged 40+ years with HIV, Vance and colleagues [55] randomly assigned 22 to receive 10 hours of speed of processing training and 24 to receive a no-contact control condition. Compared with the no-contact control group, those who received the speed of processing training improved significantly on a measure of visual speed of processing called the useful field of view (UFOV) test as well as on the timed instrumental activities of daily living test, which is a laboratory measure of everyday functioning. Related to everyday functioning, a subsequent cross-sectional driving simulator study by Vance and colleagues [13] also demonstrated that in 26 adults aged 40+ years with HIV, poorer visual speed of processing was predictive of poorer driving ability (eg, average gross reaction time, divided attention reaction time). In fact, more self-reported automobile accidents in the previous 2 years were associated with slower gross reaction time and a higher number of collisions in the driving simulator. Although this was not a cognitive training study, the results suggest that improving speed of processing may likewise improve driving in aging adults with HIV.

Targeting an intervention that specifically improves speed of processing has both theoretical and neurocognitive appeal. According to the diminished speed of processing theory [32,56-59], the rate at which adults mentally process information slows with age. Speed of processing declines can occur at all stages of processing, from the speed at which information is encoded to the execution of a response [60,61]. This reduction in speed of processing places demands on other neurocognitive systems [31]. For example, Lindenberger et al [62] found that age-related decrements in memory, reasoning, and fluency were all mediated through differences in speed of processing. A subsequent study showed that increased age affects speed of processing (effect size=−0.69) to a greater degree than memory (effect size=−0.25), or executive functioning or reasoning (effect size=−0.27), thus reinforcing the focus on speed of processing [63]. Furthermore, electrophysiological studies already indicate that adults who receive speed of processing training, compared with controls, experience increased N2pc and P3b amplitudes (electrical signals detected on the scalp), which is reflective of capacity enhancement and attentional allocation [64]. The lack of attentional and inhibition control associated with prefrontal dysregulation, especially in HIV [65,66], may be an inefficient way to process information quickly and accurately. Thus, speed of processing training may reduce dependence on frontally-oriented activity by reallocating such responses to such posterior brain regions which can improve speed of processing and in turn translate to everyday functional improvements [64,67].

Based on findings from these earlier studies, this study was proposed and funded by the National Institute of Mental Health (1R01MH106366-01A1 – “An RCT of Speed of Processing Training in Middle-Aged and Older Adults with HIV”). This randomized controlled trial (RCT) study described in this article examines a well-documented intervention in the neurocognitive and gerontological literature called speed of processing training (a cognitive remediation therapy) in the population of aging adults with HIV. Specifically, there are 3 study aims: To (1) examine whether 10 versus 20 hours of speed of processing training provides differential therapeutic responses on improving this neurocognitive ability over time; (2) examine whether 10 versus 20 hours of speed of processing training will differ in therapeutic value on improving everyday functioning (ie, IADLs, driving) over time; and (3) examine whether improvement in speed of processing and everyday functioning over time mediate improvement in quality of life indices (eg, depression, locus of control, health-related quality of life). In doing so, these 6 key areas of the study are described: (1) rationale for speed of processing training in this clinical population, (2) overview of study design, (3) eligibilty criteria and HAND, (4) intervention dosage versus control condition, (5) assessment battery, and (6) assessment of biomarkers. Finally, the complexity of this research design is examined in relation to other cognitive interventions.

## Methods

### Rationale of Speed of Processing Training

Several computerized cognitive training programs have been examined in the normal geriatric population; some focus on improving functioning in a particular neurocognitive domain such as executive functioning or memory, whereas others attempt to improve more global neurocognitive functioning. Albeit, given the resources of time and effort required to engage in training programs, selecting which neurocognitive domain to be “improved” must be chosen judiciously. Whereas some experts and clinicians may focus on memory training given its salience to noticeable memory complaints, others have found targeting other domains to have more long-lasting effects that likewise produce improvements in other areas in which training was not targeted.

In the advanced cognitive training in vital elderly (ACTIVE) study, researchers from 6 sites across the United States randomized normal, community-dwelling older adults (65+ years; N=2802) to 1 of the following treatment arms: (1) speed of processing training, (2) memory training, (3) reasoning training, and (4) no-contact control. After just 10 hours of training, those in the speed of processing training group experienced significant improvements in this neurocognitive ability. In fact, the National Institute on Nursing Research and the National Institute on Aging (January 14, 2014) announced that speed of processing training used in the ACTIVE study enabled “older people to maintain their cognitive abilities as they age,” even 10 years after training [68]. Furthermore, in a meta-analysis of 52 computerized cognitive training studies, Lampit and colleagues [52] found that treatment effect sizes varied widely depending on what neurocognitive domain was being targeted. No significant effect sizes were observed for cognitive training that targeted executive functioning or attention, whereas statistically significant small to moderate effect sizes were observed for verbal memory (g=0.08), working memory (g=0.22), nonverbal memory (g=0.24), and visuospatial skills (g=0.30), with the most robust finding observed for speed of processing training (g=0.31). These data suggest that this particular neurocognitive domain may be more amenable than others for improvement during neurorehabilitation.

To promote successful aging and optimal functioning in the aging HIV population, speed of processing is a preferred target for this cognitive training intervention based on the following points. First, speed of processing is 1 of the most essential neurocognitive abilities that declines with aging, beginning in one’s 40s [69-71]. With HIV considered as a form of accelerated aging [72,73], concerns about more profound speed of processing declines in this population increase. Second, speed of processing declines are related to poorer everyday functioning (eg, driving, performing IADLS) as well as lower quality of life (eg, health-related quality of life) [74]. Third, speed of processing training has been shown to improve this neurocognitive ability [75,76]. Fourth, this improvement in speed of processing has been shown to translate into improved driving performance, mobility, and performance on IADLs [77-83]. Fifth, in community-dwelling older adults, these neurocognitive improvements (ie, using a speed of processing measure called useful field of view) have been shown to be robust over several years; such long-term improvements may also be produced in adults with HIV. Finally, in the ACTIVE study, additional beneficial outcomes have been identified as a result of speed of processing training that include: (1) improved self-rated health [84], internal locus of control [85,86], and health-related quality of life [87-89]; and (2) protection against depression [90]. These outcomes reflect areas that must be addressed in adults with HIV who also may have reduced health-related quality of life [91-93], poor self-rated health [94], decreased locus of control [92,95-97], and depression [45,91,97,98]. These quality of life outcomes are essential areas in HIV that likewise require intervention [99]. This RCT of 264 adults with HAND extends the ability to demonstrate whether speed of processing training can improve speed of processing and everyday functioning not only in the short-term, but also during an extended 2-year period.

### Overview of Overall Study Design

A pre-post 3-group experimental longitudinal design is used (Figure 1). Participants with HAND are administered a neurocognitive, functional, and quality of life assessment battery at baseline, approximately 11-12 weeks postintervention and annually for up to 2 years. This translational science study recruits adults 40+ years with HAND and assigns them to 1 of 3 groups: (1) 10 hours of speed of processing training, (2) 20 hours of speed of processing training, and (3) 10 hours of Internet navigation training (ie, a contact-control condition).

Recruitment flyers are posted at a university HIV and acquired immunodeficiency syndrome (AIDS) clinic targeting those 40+ years only. Interested potential participants call the study telephone number to be told more about the study and to determine if they meet basic eligibility requirements (eg, HIV+, 40+ years); if they do, they are scheduled for a baseline assessment appointment. During this appointment, participants are consented and administered a neurocognitive, everyday functioning, and quality of life assessment. From this assessment, a HAND diagnosis is determined. Based on prior prevalence rates, it is expected over half of the participants experience HAND; only those with HAND and thus who need such a cognitive intervention are randomly assigned to 1 of the 3 treatment arms. Block stratified random assignment will minimize the risk of imbalance among randomized groups in 2 key factors: minority status and speed of processing deficiency measured by a cut off using the useful field of view test [100]. Completion of each arm should take participants approximately 10 weeks. After training, participants are administered the same baseline assessment at posttest and then annually for 2 years. Two years of follow-up is justified because it is needed to determine the robustness of the speed of processing training over time in this clinical population as observed in the older adults in the ACTIVE study. To retain participants over a 2-year period, several strategies are employed; here are a few examples: (1) sending reminder holiday and birthday cards to participants; (2) providing little gifts to participants with the study name, phone number, and logo on them; and (3) gathering information on secondary contacts of people they know so we can track them down in case such participants move. In addition, participants are compensated for their time they spend with the study.

**Figure 1 figure1:**
[figure not shown]
Overall study design flowchart.

### Recruitment Protocol, Rationale, and Targeting HAND

Eligibility criteria specifically focus on casting a wide net to ensure that the study findings are generalizable to the larger HIV population. Albeit, given the focus on driving and neurocognition, certain inclusion, exclusion, and HAND criteria were chosen.

#### Inclusion Criteria

Since driving-related factors are being examined as 1 of the outcomes of the intervention, participants must be licensed drivers when entering the study. Otherwise, participants (men and women) must be 40+ years, English-speaking, and have HAND.

#### Exclusion Criteria

Due to this study being longitudinal, participants not living in stable housing (eg, halfway house) are excluded because of the challenge of scheduling follow-up visits. Potential participants are excluded if they indicate that they are planning to move away from the Birmingham metropolitan area within the next 2 years. Furthermore, participants with significant neuromedical comorbidities (eg, schizophrenia, epilepsy, bipolar disorder, multiple sclerosis, Alzheimer disease or related dementias, mental retardation) are excluded; such major neurological comorbidities may confound study results and interfere with the cognitive training. These comorbidities are assessed in the telephone screen and confirmed after the baseline assessment using the university HIV and AIDS Clinic electronic medical charts. Other conditions (eg, legally blind or deaf [vision confirmed at baseline], currently undergoing radiation or chemotherapy, a history of brain trauma with a loss of consciousness greater than 30 minutes) that could impact neurocognitive functioning or testing also necessitates exclusion; again, this information is conferred in the telephone screen and again at baseline. These typical exclusion criteria are used in many HIV neurocognitive studies [12,14,101-104]; we wish to exclude those with other major neurological conditions besides HIV that affect neurocognition.

### HIV-Associated Neurocognitive Disorders

This study focuses on HAND and speed of processing training. Typically, speed of processing declines emerge in one’s 40s [70] and perhaps even earlier for those with HIV, which likely contributes to HAND [73]. In fact, the prevalence of HAND may be greater in middle-aged and older adults with HIV [12,18,105,106]. Primary reasons for the focus on HAND are: (1) participants have room to improve neurocognitively from speed of processing training (ie, no ceiling effects), and (2) a cognitive intervention for HAND is needed. Using a neurocognitive battery that measures performance in several neurocognitive domains, the Frascati criteria is used to determine HAND [104]. If a participant’s neurocognitive scores are greater than 1 standard deviation below demographically-adjusted means in at least two neurocognitive domains (eg, memory, speed of processing), they are determined to have HAND. Further breakdown of the type of HAND diagnosis can be made based upon functional impairment too (ie, Lawton and Brody activities of daily living) to compare differences in treatment response for those with varying severity of HAND. In consensus, 2 doctorally-trained psychologists determine HAND based upon the demographically adjusted *t* scores.

### Intervention Dosage Versus Control Condition

Both the speed of processing and contact-control training protocols require participants to visit the laboratory to engage in 1-hour sessions with passive supervision from a research assistant. The research assistant greets participants, helps them log onto the computer, answers questions participants may have about the training, and monitors the time participants engage in their assigned treatment arm.

In the speed of processing training protocol, participants are trained to improve the speed or accuracy in which they identify and locate visual-spatial information using 5 games or exercises from the POSIT Science, which has been used in our prior studies. The games include: (1) Sweep Seeker (fundamental speed of processing), (2) Bird Safari (visual accuracy), (3) Target Tracker (multiple object tracking), (4) Master Gardener (eye movements), and (5) Double Decision (UFOV). These games are automatically customized to the participants’ individual ability. The speed, difficulty, and complexity of each game is systematically increased as participants successfully master specified performance criteria. Manipulations used to increase difficulty include decreasing the duration for which the visual stimuli are presented, adding visual or auditory distracters, increasing similarity between targets or distracters, and presenting visual targets over a broader spatial expanse, which expands one’s (UFOV) and is important for driving [107].

Studies using speed of processing training often vary from 10 to 20 hours. As mentioned in the prior study in adults with HIV, 10 hours of training was sufficient to produce significant improvement in UFOV and everyday functioning in the short-term. The NIH-funded ACTIVE study (N=2802 normal older adults) also initially used 10 hours of speed of processing training, but additional “booster” training was found to improve the effect size and these improvements were robust over several years [108]. A meta-analysis [52] of cognitive training in older adults found specifically for speed of processing training, a dose of 20 hours or less produced a significantly higher effect size (0.34) compared with more than 20 hours (0.24). Given these dosage considerations, in this study 1 treatment arm receives 10 hours of training and 1 treatment arm receives 20 hours of training, whereas the control arm of the study will receive 10 hours of nontherapeutic computer contact. This approach will allow our study to determine the optimal therapeutic dosage over time. Likewise, conclusions from this meta-analysis [52] suggest that optimal effect sizes from speed of processing training for our study will be observed when training sessions are at 60 minutes and administered 1-3 times per week—dosage parameters already incorporated in this study.

In the contact-control group, participants receive 10 hours of Internet navigation training; it has been used successfully as an optimal social or computer contact-control condition for speed of processing training studies. This contact-control (sham) condition mirrors speed of processing training with the same amount of social contact with study staff and computer exposure, but does not provide any therapeutic neurocognitive benefit as we have previously observed [75,81,109]. Specifically, participants are given instructional materials and exercises on how to navigate the Internet. For more computer savvy participants, they are directed to other websites that may be of interest. These Internet activities reflect those which people do normally and do not have any observable neurocognitive therapeutic effect. This approach has been used in prior National Institute on Aging-sponsored studies [75]. This contact-control group is being used to compare with the other intervention in which only 10 hours of the speed of processing training are being provided; this will allow for a direct comparison. Meanwhile, the intervention with 20 hours of training is being included to test whether the extra dosage will be more effective versus 10 hours of speed of processing training alone.

Finally, a treatment fidelity checklist is used so staff can review with participants the amount of time that they have engaged in training. Furthermore, the POSIT Science software monitors the amount of time participants spend engaged in each exercise. As in the ACTIVE study, participants are considered to be trained when they successfully complete 80% of the training [107]. This completer-only analysis is appropriate for use when examining the actual potential of the speed of processing training. If participants do not complete training, their data can be examined using an intent-to-treat analysis.

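### The article endorses a completer-only analysis with unequal hour thresholds (8 versus 16 hours) and misdescribes intent-to-treat, so a dose comparison made that way is not protected by randomisation

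*Protocol article*

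**What the plan says.** The section Intervention Dosage Versus Control Condition holds the article's only statements on who is analysed. The completion rule is that "participants are considered to be trained when they successfully complete 80% of the training". On the set so defined, the article says: "This completer-only analysis is appropriate for use when examining the actual potential of the speed of processing training". The next sentence reads: "If participants do not complete training, their data can be examined using an intent-to-treat analysis". Neither analysis is called primary.

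The arms to which the rule applies are listed under Overview of Overall Study Design as "1) 10 hours of speed of processing training, (2) 20 hours of speed of processing training, and (3) 10 hours of Internet navigation training". Sessions last one hour, and the same section says: "Completion of each arm should take participants approximately 10 weeks". The first aim, in the Introduction, is to "examine whether 10 versus 20 hours of speed of processing training provides differential therapeutic responses on improving this neurocognitive ability over time"; the second aim asks the same dose question of everyday functioning.

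**The concern.** Two things are stated badly.

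First, intent-to-treat is attached to the wrong people. It is an analysis of all randomised participants in the arm to which they were assigned. The article makes it optional and ties it to the data of those who do not finish. An analyst who followed the two sentences literally would have completers in one analysis and would have no instruction to analyse everyone as randomised.

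Second, completion happens after randomisation, and it may go with motivation, health and cognition, which also bear on the outcomes. A comparison of completers is then a comparison of self-selected groups. The filter is also not the same in each arm, because a fixed percentage of unequal doses gives unequal hours. Someone in the 20-hour arm who stops at 12 hours counts as not trained, while someone in the 10-hour arm who stops at 8 hours counts as trained. The contrast affected is the one between doses, from which the article wants to learn the best training dose. The block-stratified randomisation on minority status and useful-field-of-view deficiency does not protect a comparison restricted in this way.

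**Working it through.** The article gives no completion rate, dropout rate or adherence-outcome correlation, so there is no figure of its own to reproduce. The thresholds follow from the document. The bias can only be shown under assumptions.

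**Thresholds (from the article)**
- 10-hour training and 10-hour control: 0.80 × 10 = 8 hours.
- 20-hour training: 0.80 × 20 = 16 hours.
- With one-hour sessions and about 10 weeks per arm, the full course is about 10/10 = 1 session a week against 20/10 = 2 a week.

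**Completion (assumed)**
Take a constant 2% dropout per one-hour session, with 1% to 3% as the range.
- 2%: 0.98^8 = 0.851 and 0.98^16 = 0.724.
- 1%: 0.99^8 = 0.923 and 0.99^16 = 0.851.
- 3%: 0.97^8 = 0.784 and 0.97^16 = 0.614.

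**Selection bias with no true dose effect**
Let the outcome (SD 1) have correlation ρ with a latent normal adherence score, and let each arm keep its top fraction c. The completers' mean is ρ × m(c), where m(c) = φ(z)/c and z is the normal quantile at 1 − c. The bias in the 20-minus-10-hour difference is ρ × [m(c20) − m(c10)].

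At 2% dropout:
- m(0.851) = 0.2324/0.851 = 0.273.
- m(0.724) = 0.3344/0.724 = 0.462.
- Difference 0.189. With ρ = 0.2 the bias is 0.038 SD; with ρ = 0.5 it is 0.094 SD.

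Over the 1% to 3% range, the difference in m runs from 0.115 to 0.249. The bias therefore runs from 0.2 × 0.115 = 0.02 SD to 0.5 × 0.249 = 0.12 SD.

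**When the direction changes**

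| Completion 10 h / 20 h | ρ | Bias, 20 h minus 10 h (SD) | Two-sided type I error at nominal 0.05 |
|---|---|---|---|
| 90% / 90% | any common value | 0.00 | 0.050 |
| 90% / 80% | 0.1 to 0.5 | +0.015 to +0.077 | 0.051 to 0.076 |
| 90% / 70% | 0.1 to 0.5 | +0.030 to +0.151 | 0.054 to 0.144 |
| 90% / 70% | −0.3 | −0.091 | 0.083 |
| 80% / 90% | 0.3 | −0.046 | 0.059 |

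The type I error column uses 88 × c completers per arm. It takes 264/3 = 88 as the arm size, which assumes equal allocation; the article does not state the ratio.

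For scale, the meta-analysis cited under Rationale of Speed of Processing Training puts the effect of speed of processing training at g = 0.31. The figures above are between-arm biases in a dose contrast, not shares of that effect.

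**After the fix**
With everyone analysed as randomised, the 80% rule selects nobody. Its contribution to bias is zero, apart from any bias from missing outcome data.

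**The case against.** The strongest reply is that the article restricts the completer analysis to a narrow, explanatory purpose, leaves intent-to-treat available and excludes nobody from every analysis. The intent-to-treat sentence can be read charitably as saying that non-completers' data enter through that analysis. The posttest and annual assessments are not limited to completers. A full protocol or analysis plan, not shown, may name the primary set.

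Much of this stands. A reader might infer that completers are the fixed main analysis, and the text does not say so. The absence of a named primary set is not the complaint either. What remains is what the article does say: a wrong account of intent-to-treat, and approval of a set whose threshold differs between the arms to be compared.

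Four further inferences are tempting and are not supported:

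- **The rule favours 20 hours.** That needs lower completion at 20 hours together with better outcomes among adherent people. The doubled weekly burden makes lower completion plausible, but the documents give neither quantity.
- **Completion is measured differently in the control arm.** It is true that "the POSIT Science software monitors the amount of time participants spend engaged in each exercise", but the article describes both protocols together when it says that a research assistant monitors time in the assigned arm. The fidelity checklist is not limited to the training arms, and nothing makes the software log the sole arbiter.
- **Completer selection creates a spurious benefit of 10 hours over control.** Those arms share the 8-hour threshold. With the same dropout and correlation, the model above gives zero.
- **A complier-average estimate with randomisation as instrument would solve it.** That requires assignment to have no effect in people below 80%. Someone with 12 of 20 hours has had substantial training, so the requirement is doubtful.

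**Conclusion.** The point holds in this form: the article misdescribes intent-to-treat, and it endorses a completer set defined by 8 hours in one training arm and 16 in the other. A 10-versus-20-hour comparison in that set is open to selection bias of unknown direction and size.

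Under assumed completion of 85% versus 72% and an assumed adherence-outcome correlation of 0.2 to 0.5, the bias is about 0.04 to 0.09 SD in favour of 20 hours. It is 0.02 to 0.12 SD if dropout per session is 1% to 3%. It vanishes with equal completion and a common correlation, and changes sign if 20-hour completion is the higher or the correlation is negative. The thresholds and the misdescription come from the document; every bias figure rests on assumptions. The distortion is modest in most of these scenarios, but it falls on the trial's central contrast and is easily avoided.

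**What to change.** Replace the two sentences on completer-only and intent-to-treat analysis with text to this effect:

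- The primary analysis of Aims 1 to 3 includes all randomised participants in their assigned arm, whatever number of training hours they completed.
- All randomised participants are assessed at posttest and at both annual visits, including those who stop training.
- The comparison among participants with at least 80% of assigned training is supportive only. It is reported with the hour threshold (8 or 16) and the number completing in each arm, and with a statement that it is not a randomised comparison.

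The cost is two rewritten sentences, an estimate that may be smaller than the completer estimate, and follow-up of people who stop training. The article already plans two years of retention effort for participants in general and reports enrolment as ongoing, so the change could be made before results are known.
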